### Ethical Considerations

This trial was registered in the Chinese Clinical Trials Registry in 2023 (ChiCTR2300070289). The ethics committee of the Third Affiliated Hospital of Henan University of Chinese Medicine has approved this study protocol (ethics approval number 2022HL-031).

This RCT will adhere to the ethical principles governing biomedical research on human participants and respect fundamental human rights in accordance with international recommendations included in the Declaration of Helsinki and its subsequent revisions.

Participants will be given both written and oral information about why the trial will be conducted, its objectives, the potential risks associated, and the guidelines set out during the monitoring period. If a patient fulfills the inclusion criteria and agrees to enroll in the trial, they will provide written informed consent. Patients are free to withdraw consent and discontinue the trial at any time and for any reason.

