## Methods

### Trial Design

Patients will be recruited through advertisement in the Tuina clinic of the Third Affiliated Hospital of Henan University of Chinese Medicine, Zhengzhou, China. We will follow the SPIRIT (Standard Protocol Items: Recommendations for Interventional Trials) 2013 statement [16] to guide the reporting and development of our protocol. All eligible participants will be required to sign an informed consent form and will be notified that the trial will not contain any collection of human biological specimens.

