**Figure 1 figure1:**
[figure not shown]
Flowchart of the trial. fMRI: functional magnetic resonance imaging; HAMD: Hamilton Depression Scale; NRS: Numerical Rating Scale; PPT: pressure pain threshold; WOMAC: Western Ontario and McMaster Universities Osteoarthritis Index.

**Table 1 table1:** Chart of the trial’s time points.

Research process	Enrollment	Allocation	Beginning	End of the experiment
Eligibility screen	✓			
Demographic variables	✓			
Medical variables	✓			
Allocation		✓		
Consent			✓	
fMRI^a^ scan			✓	✓
PPTs^b^			✓	✓
NRS^c^			✓	✓
HAMD^d^			✓	✓
WOMAC^e^			✓	✓
Adverse events			✓	✓
Working practice record			✓	✓

^a^fMRI: functional magnetic resonance imaging.

^b^PPT: pressure pain threshold.

^c^NRS: Numerical Rating Scale.

^d^HAMD: Hamilton Depression Scale.

^e^WOMAC: Western Ontario and McMaster Universities Osteoarthritis Index.

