### Randomization

Independent research staff will use SPSS 25.0 (IBM Corp) to generate a randomly numbered sequence for complete randomization. Participants will be randomly assigned into 1 of 2 groups (ie, health education or Tuina group) and applied in a 1:1 allocation ratio. The random sequence will be sealed by a self-governing research assistant via an opaque envelope that contains information regarding the participant’s allocation.

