### Blinding

The outcome evaluators and data statisticians will all be masked to the group assignment to prevent bias.

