### Interventions

A panel of 2 clinical medical professionals with an academic background in Tuina and clinical medicine agreed to develop a standard protocol for Tuina and health education. The protocol’s feasibility will be examined to determine whether it is practicable and acceptable and to identify any realistic issues caused by the procedures. Given the nature of the treatment, participants will be informed that the trial will be without harm, compensation, and posttrial care.

Clinical medical professionals with ≥3 years of experience with Tuina will conduct the health education for the participants. Before the trial, clinicians will be trained to ensure standard procedures and compliance with treatment protocol. All participants in the Tuina group will receive three 20-minute sessions a week over a 6-week treatment course. The participants in the health education group will participate in health education sessions lasting 1 hour each (administered once weekly for 6 weeks). The participants are to maintain their dietary habits and regular physical activity throughout the study period. Throughout the trial, they will be informed that they are not permitted to entertain other remedies. To guarantee compliance, all participants are required to register for therapy in a written log.

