### Numerical Rating Scale

The NRS is an elementary well-managed scale to assess pain intensity. Patients express the intensity of rest and movement pain using the numbers 0-10.

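### Table 1 puts consent and all baseline outcome assessments after allocation, while the ethics section ties consent to enrolment

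*Protocol article*

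**What the plan says.** Two places in the text describe consent. Trial Design states: "All eligible participants will be required to sign an informed consent form". Ethical Considerations is more specific about the moment: "If a patient fulfills the inclusion criteria and agrees to enroll in the trial, they will provide written informed consent". Both attach consent to eligibility or enrolment; neither mentions randomisation.

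Table 1 has this header: "Research process Enrollment Allocation Beginning End of the experiment". The eligibility screen, demographic variables and medical variables are ticked under Enrollment, and allocation under Allocation. Consent has a single tick, under Beginning. The fMRI scan, PPTs, NRS, HAMD and WOMAC are ticked under Beginning and again at the end.

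On concealment, the Randomization section says: "The random sequence will be sealed by a self-governing research assistant via an opaque envelope that contains information regarding the participant’s allocation". On masking, the Blinding section says: "The outcome evaluators and data statisticians will all be masked to the group assignment to prevent bias". Participants are not included, and Limitations and Strengths concedes that blinding is difficult with these interventions. The Methods part of the Abstract commits the main analyses to intention to treat.

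**The concern.** The table and the ethics text give different moments for consent, and site staff cannot follow both. If the table is followed, people are allocated before they have agreed to take part. Someone who then learns the arm and declines has been randomised but may contribute no data, and the reason for the loss can depend on the arm. That is plausible here, because recruitment runs through a Tuina clinic and the comparator is health education. Such losses would damage the comparability that intention to treat is meant to protect.

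The second issue is the baseline. If outcomes are first measured after allocation, and the participant has been told the arm, the baseline is no longer independent of treatment assignment. Masking the assessor does not repair this where the value comes from the participant's own judgement.

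**Working it through.** No arithmetic applies. The check is a comparison of the table with the text.

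**Step 1. Tick positions in Table 1 (first tick for each row).**

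| Row | Enrollment | Allocation | Beginning |
|---|---|---|---|
| Eligibility screen | ✓ | | |
| Demographic variables | ✓ | | |
| Medical variables | ✓ | | |
| Allocation | | ✓ | |
| Consent | | | ✓ |
| fMRI, PPTs, NRS, HAMD, WOMAC | | | ✓ |

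The positions are consistent across rows: Consent lines up with the outcome rows and not with the screening rows. An error in reading the table from the PDF is therefore unlikely.

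**Step 2. Table against text, on consent.** Ethical Considerations places consent where an eligible patient agrees to enrol, which is the first column. Table 1 places it in the third. This is a direct conflict. As tabulated, the medical variables, which the Demographic or Medical Variables section says include K-L score, blood pressure and medication, are also collected before consent.

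**Step 3. Table against text, on baseline outcomes.** Ethical Considerations is silent here, so there is no contradiction. MRI Data Acquisition and Clinical Outcome Assessments place the first assessments at the beginning of the experiment, the term that heads Table 1's post-allocation column. No section states that they precede allocation, so the table's order stands uncorrected.

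**Step 4. Could the participant know the arm at baseline?** The Randomization section describes a sealed opaque envelope but does not say when it is opened or when the participant is told. The Blinding section does not cover participants. The stated plan therefore permits such knowledge without establishing it.

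**Step 5. Which measures are exposed?** The NRS is the participant's own rating: "Patients express the intensity of rest and movement pain using the numbers 0-10". The PPT reading ends when the participant reports pain. Both depend on the participant whoever records them. For resting-state connectivity, an effect of expectation is conceivable but not shown. For grey matter volume the document offers no argument for one.

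**Step 6. Where does the baseline enter the analysis?** The Ranked Data and Count Data section plans within-group Wilcoxon comparisons of NRS and WOMAC, which use the baseline directly. It also plans between-group Mann-Whitney tests, without saying whether these use end scores or changes. If they use end scores only, a shifted baseline adds no bias to them.

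**The case against.** The strongest reply is that this is a misplaced tick. Both text sections tie consent to eligibility or enrolment, the envelope is sealed, and Figure 1, which shows the flow from recruitment to randomisation, is not available in the copy reviewed. An article also commonly leaves envelope handling to the full protocol. Much of this stands: a layout slip is at least as plausible as an intention to randomise before consent, and a missing sentence on envelope opening would not be a finding by itself. But the article does state a sequence in its only tabulated schedule, that sequence conflicts with its own ethics section, and nothing shown corrects it.

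A reader might infer several stronger things that the document does not support:

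- **That every baseline measurement follows allocation.** Rows such as "Demographic variables" and the medical variables are ticked under Enrollment, and the NRS entry criterion implies a pain score at screening. Only the baseline outcome assessments come later.
- **That the ethics section contradicts the baseline order.** It conflicts with Table 1 on consent alone.
- **That participants do know their arm at baseline.** The time of disclosure is not stated.
- **That the bias can be given a size.** This would require an assumed shift in scores or number of refusals, and a change-score or baseline-adjusted analysis that the article does not name.

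**Conclusion.** The point holds as a conflict over when consent is given, together with a tabulated order that puts all baseline outcome assessments after allocation. It rests on three facts: the tick positions in Table 1, the consent wording in Ethical Considerations, and a masking statement that leaves participants out. The consequences (arm-dependent refusal after allocation, and participant-dependent baselines given with knowledge of the arm) are risks the schedule permits. Whether either occurs depends on when envelopes are actually opened, which is not stated, so no magnitude is claimed.

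One neighbouring statement is a separate matter. Under Interventions, "participants will be informed that the trial will be without harm, compensation, and posttrial care". The phrase is garbled, may concern only compensation and care arrangements, and does not bear on the order of consent and allocation. Read literally, it sits badly with the side effects listed under Exit Criteria and Management, the recording of adverse events, and the promise in Ethical Considerations to explain potential risks. Those passages need reconciling in their own right. No effect of that wording on adverse-event reporting can be inferred.

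**What to change.** - In Table 1, move Consent to the Enrollment column, ahead of any study procedure, so that it agrees with Ethical Considerations.
- Place the baseline fMRI, PPT, NRS, HAMD and WOMAC before Allocation.
- Add a sentence to the Randomization section stating that the envelope is opened only after consent and the baseline outcome assessments are complete.
- Enrolment began in December 2023, so for those already enrolled, document the actual order of consent, baseline assessment and allocation. If anyone was allocated before consent or before baseline, report the number by arm and a sensitivity analysis excluding the affected participants.

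The cost is small: a corrected table, one sentence, and a record check. The downside is a few baseline scans in people who then are not randomised. If Table 1 is only a layout slip, the correction changes nothing in conduct, and the record check will confirm it.

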## Results

This trial was approved by the ethics committee of the Third Affiliated Hospital of Henan University of Chinese Medicine. Enrollment began in December 2023, and the results of this trial are expected to be submitted for publication in May 2025.

## Discussion

### Overview

To the best of our knowledge, our trial will be the first to assess the modulatory effect of Tuina on the descending pain inhibitory system in patients with KOA. The results will improve the apprehension regarding Tuina’s mechanisms in patients with KOA.

KOA can cause joint dysfunction, reduce physical fitness and capability to tackle activities of daily living, and cause depression and anxiety [3,34,35]. Previous researchers have indicated that peripheral factors such as synovial inflammation and articular cartilage devastation may have a cardinal role [36-38]. However, many studies found that the severity of radiographic KOA and the inflammatory response of the synovial membrane do not positively correlate with KOA [39-41]. Consequently, peripheral mechanisms cannot completely explain KOA. Patients with KOA have simultaneously raised pain sensitivity in affected and nonaffected areas. Therefore, some investigators suggest that an “abnormal central processing” of afferent pain messages may be a cardinal factor in KOA [26].

Based on the theory of traditional Chinese Tuina, all the acupoints can treat the disease of the adjacent area and local area. In our study, 6 local acupoints are selected in the Tuina group, including Xuehai (SP10), Yinlingquan (SP9), Yanglingquan (GB34), Liangqiu (ST34), Xiyan (EX-LE5), and Zusanli (ST36). Yanglingquan (GB34) and Yinlingquan (SP9) are also known as the converging point of the tendon footprint and are usually recommended to relieve knee pain. Xuehai (SP10) and Liangqiu (ST34) are the most commonly used acupoints for the treatment of dysfunction caused by KOA. Xiyan (EX-LE5) is supplemented to adjust the tension of soft tissue. Zusanli (ST36) is commonly used for the treatment of inflammation and pain. Our previous results showed that the above 6 acupoints used together can effectively improve the pain of patients with KOA [7].

Moreover, Tuina is safe and effective for pain, physical function, stiffness, and other clinical symptoms associated with KOA [42]. It likewise has been demonstrated to activate and modulate functional connectivity in the hippocampus to facilitate cognitive function in patients with poststroke depression [43]. The brain has a powerful control over nociceptive input in the spinal cord at the brain stem level. This top-down control occurs through the “descending modulation” of the pain transmission pathway mechanism [44-46]. The descending pain inhibitory system has a cardinal role in normal pain consciousness, and its malfunction may be one of the pathophysiological mechanisms in KOA. This factor possibly clarifies how other centrally mediated processes, such as sleep, mood, the placebo effect, and cognition, influence the pain experience [47]. Crucially, the PAG and RVM, as important components of the descending pain inhibitory system, directly modulate the activity of the spinal neurons involved in pain transmission [48]. Furthermore, animal experiments have demonstrated that the PAG is involved in opioid-mediated analgesia since the microinjection of morphine into this nucleus produces a reduction in sensory pain behaviors [49]. Similarly, the analgesic effects of stimulating the PAG directly have also been evidenced in humans [50]. Moreover, direct PAG stimulation is used to diminish chronic pain intensity in individuals [51]. The RVM is the pontomedullary area where opioid microinjection generates analgesia [48]. Making allowances for this, the PAG-RVM axis, as a significant component of the descending pain inhibitory system, can possess an inhibitory implication on harmful transmission. However, the mechanism of the descending pain inhibitory system in the analgesic effect of Tuina in the treatment of KOA is unclear, especially the relationships among PAG and RVM and clinical behavioral indicators, which limits its promotion and application. Therefore, fully exploring the central analgesic mechanism is necessary to alleviate the pain of KOA. As a main type of fMRI, resting-state fMRI has the advantage of providing more comprehensive information on the functional architecture of the brain. Resting-state fMRI is widely used to study the analgesic mechanism of Tuina in the treatment of KOA [52].

In summary, this clinical trial will aim to investigate the influence of Tuina on the descending pain inhibitory system in order to explain the potential central mechanism of Tuina treatment. We will use a combination of resting-state MRI and clinical behavior indicators such as rsFC and VBM to perform research and analysis of Tuina analgesia.

### Limitations and Strengths

Although this study’s potential strengths, it anticipates limitations. First, there is potential for methodological bias, as blinding is particularly difficult when delivering a physical intervention or health education. Second, the long-term implications of Tuina will not be investigated; thus, further research is warranted. Despite these several different limitations, this study’s strengths lie in its focused investigation of the potential central mechanism of Tuina treatment, which contributes valuable insights into the modulatory effect of Tuina on the descending pain inhibitory system in patients with KOA.

### Conclusions

This trial is designed to investigate the central mechanism of Tuina in the treatment of KOA, with the involvement of health education as a control intervention. We expect that Tuina would relieve pain symptoms in patients with KOA and that pain relief would be associated with the descending pain inhibitory system.

## Abbreviations

CRF: case report form
CSF: cerebrospinal fluid volume
DARTEL: Diffeomorphic Anatomical Registration With Exponentiated Lie Algebra
fMRI: functional magnetic resonance imaging
FOV: field of view
GMV: gray matter volume
HAMD: Hamilton Depression Scale
K-L: Kellgren and Lawrence
KOA: knee osteoarthritis
MRI: magnetic resonance imaging
NRS: Numerical Rating Scale
PAG: periaqueductal gray
PPT: pressure pain threshold
RCT: randomized controlled trial
ROI: regions of interest
rsFC: resting-state functional connectivity
RVM: rostral ventromedial medulla
SPIRIT: Standard Protocol Items: Recommendations for Interventional Trials
SPM: statistical parametric mapping
VBM: voxel-based morphometry
WM: white matter
WOMAC: Western Ontario and McMaster Universities Osteoarthritis Index
